#### 2.6.5. Management of Results

Results are reported by the laboratory that performed the testing using a standardized study report template. The report for the reproductive couple conveys either that the couple has a low chance of having children with conditions associated with any of the genes screened, or the couple has an increased chance of having children with one or more conditions. The results of carrier status for each individual within the reproductive couple are not issued and only the combined result for the reproductive couple.

Results indicating a low chance of conditions associated with any of the genes screened are issued to the rHCP by fax, secure email or mail. Both reproductive partners are notified via email that the result has been uploaded to the secure online participant portal. They are then able to use their individual login details to access their report and a factsheet explaining their low chance result. Participants have the option of discussing their result with a study genetic counselor. For those who enrolled via a modified enrollment pathway, the result is provided by a study genetic counselor (with an interpreter as required). Where necessary, correspondence is translated into the relevant language.

When the results indicate an increased chance for one or more of the conditions screened, a study genetic counselor contacts the rHCP to discuss the result. The couple is then contacted directly by the genetic counselor. The genetic counselor discusses the result with the couple by telephone and offers a genetic counseling consultation as soon as practicable, either face-to-face or via telehealth. When participants using one or more donor(s) receive an increased chance result, genetic counseling is available to all involved parties, including those who are not the genetic parents of the current or planned pregnancy but who would be parenting the child. The genetic counseling consultation (provided by a genetic counselor, with a clinical geneticist if required) includes a discussion of the clinical features of the condition, the implications of the result, reproductive options and implications of the information for relatives, including current children, if relevant. The study genetic counselors assist people in adjusting to their knowledge of the results and support their decision-making regarding their reproductive options. If appropriate, access to subspecialists with expertise in the condition is also available (e.g., a pediatric respiratory physician for cystic fibrosis, a pediatric neurologist for spinal muscular atrophy, etc.) and, as available, to the support organization for the relevant condition. A copy of the result is provided to the couple either before, during or after their genetic counseling consultation via email/mail/in person, in line with standard clinical practice.

A range of reproductive options is discussed with and offered to participants who receive an increased chance result, including: PND by chorionic villus sampling or amniocentesis (with the option of pregnancy termination if affected), IVF with PGT-M, using donor gametes/embryos (with RGCS for the donors), adoption/fostering, choosing not to have children/more children or choosing not to have any testing. For MM increased chance couples, PND and PGT-M are available at no charge to the couple so that the study can assess reproductive choices when cost is not a barrier. Funded PND is provided through the Australian public healthcare system and one cycle of IVF with PGT-M is funded through the study in partnership with local IVF services. For all increased chance couples, the local study clinical team provide comprehensive clinical support around the consideration of each of these options as well as psychosocial support, referral to specialists if there are considerations regarding pregnancy management, referral for the termination of pregnancy if requested, or testing, clinical assessment and management of the baby after birth.

Increased chance couples are asked to complete a survey before and after genetic counseling (T3a, Table 3). Approximately three months post result, all participants are invited to complete an online survey, and again approximately 12 months post result (T3 and T4, respectively, Table 3). Subsets of participants are also invited to take part in a semi-structured interview at either of these timepoints.

### 2.7. Phase 3—Post-Implementation: Assessing Outcomes

Phase 3 will commence in the second half of 2022 and will involve an analysis of the quantitative and qualitative data, and ultimately will report the study findings to the Australian Government. The results are informing an application for publicly funded expanded RGCS in Australia which has been submitted through the Medical Services Advisory Committee (MSAC) [65], an entity that advises the Australian Minister for Health on tests that should be funded through Medicare, the publicly funded universal healthcare insurance scheme in Australia.

#### 2.7.1. Proposed Analysis

This observational study involves a mixed-methods approach, integrating data from across the psychosocial and epidemiology, implementation science, and health economics research streams, to assess the acceptability and feasibility of the developed RGCS program. An effort has been made to capture a wide variety of attitudes and views, including of those who decline the offer of RGCS. These findings will be presented against the background of the bioethics analysis, which has been undertaken throughout the project.

##### Quantitative Analysis

Quantitative data will be analyzed using the statistical software packages, STATA 16 and SPSS. Descriptive statistics will be used to summarize the program outcomes including the RGCS uptake, frequency of increased chance couples and reproductive decisions made by these couples. Detailed participant characteristics will be reported, with the representativeness of the participant sample compared to Australian population data assessed using a minimum dataset (e.g., socioeconomic status via the Index of Relative Advantage and Disadvantage quintile).

Data will be summarized using descriptive statistics (e.g., means, standard deviations, medians, interquartile ranges, frequency distributions and 95% confidence intervals). Inferential analysis will include univariable analysis such as χ^2^ and Fisher exact tests, unadjusted logistic regressions for categorical outcomes, and independent, two-tailed *t*-tests or non-parametric Mann–Whitney U tests for continuous outcomes. A comparison between participants who had RGCS and participants who did not proceed with RGCS after initiating enrollment will be performed using multivariable logistic regression, adjusting for significant covariates (*p* < 0.1 in the univariable analysis).

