#### 2.5.4. Developing the Enrollment and Participation Process

An online participant portal, including the education module and decision aid, was designed as a convenient way for couples who were invited to take part in the study by their rHCP to enroll and participate. The participant portal was designed by the digital health technology company, Curve Tomorrow, based on the design of the Australian Genomics dynamic consent platform, ‘CTRL’ [43], and with involvement from the MM study team. The participant portal is a web application accessible from smartphones, tablets and computers. Information entered into the participant portal is automatically transferred into the MM electronic study database. Each couple accesses the portal with a unique access code, linked to their rHCP. This access code is provided by the rHCP on a study invitation form (see Supplementary File S2) either in hard copy or electronically. On one side of the invitation form is a brief description of the study and instructions for how to access the participant portal, and on the reverse, is a test request form which is completed by the rHCP to be used for those who accept RGCS. 

To capture the breadth of views on RGCS, the portal was designed to allow for the participation of: those who want to have the screening, those who do not, and those who are unsure. The portal includes: a short introductory video on the study; eligibility questions; a provision of consent to participate in the research; a collection of demographic information; the education module; the optional decision aid [42]; clinical consent for RGCS; an evaluation survey; and optional dynamic consent preferences for data sharing. 

Consent for undergoing RGCS is separate from the consent to take part in the research study, so that the RGCS consent can be provided after the participant has viewed the education module and engaged with the decision aid. The RGCS consent process includes: the purpose of screening; limitations; possible outcomes; the use of information gained through the genetic carrier screening; and data sharing for research. Optional consent preferences for data sharing with other research studies were adapted from the Australian Genomics CTRL platform [43], using a dynamic approach which allows participants to revisit the participant portal and change their preferences at any time.

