#### 2.6.3. Enrollment

For those wanting to participate in the study, one member of the couple accesses the online participant portal via a web link and enters the unique access code provided on the study invitation form. They are then asked to complete questions to assess their eligibility for the study. If the couple does not meet the eligibility criteria, the portal indicates they are not eligible to take part in the study and are unable to proceed further. If the couple meets the eligibility criteria, the participant is prompted to create an account in the portal. They are then asked to provide the contact details of their reproductive partner, who is automatically emailed a link to create their own account in the participant portal. Both reproductive partners complete the full enrollment process in parallel in their own time; this can be completed in one sitting, or participants can log back into the portal to complete their enrollment later. All participants, regardless of whether they choose to have a screening, complete a set of questions for the program evaluation (T1, Table 3). For a couple to access RGCS through the study, the full enrollment process must be completed by both reproductive partners. A small number of purposively sampled participants who commenced enrollment in the study have been invited to take part in an interview (Table 3).

As shown in Figure 3, there are several points in the study at which participants may drop out of or be lost to follow-up during the enrollment and/or RGCS process. Follow-up is undertaken via email reminders and, if necessary, a phone call from a study genetic counselor. If contact is made and reasons for the incomplete enrollment are noted, participants are recorded as having chosen not to complete enrollment. If enrollment is completed but the RGCS mouth swab kit is not returned, the couple is recorded as having chosen not to complete RGCS. Couples who provide research consent but do not complete the enrollment or RGCS process are still able to be invited to participate in MM research activities (e.g., interviews) unless they request no further contact.

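### Having RGCS is decided for the couple, but the uptake comparison counts individual participants with no allowance for partners sharing the same outcome

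*Protocol article*

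**What the plan says.** **Unit and model.** Section 2.7.1, Quantitative Analysis: "A comparison between participants who had RGCS and participants who did not proceed with RGCS after initiating enrollment will be performed using multivariable logistic regression". Covariates enter the model if p < 0.1 in univariable analysis. The univariable methods are described as "univariable analysis such as χ^2^ and Fisher exact tests, unadjusted logistic regressions for categorical outcomes", with t-tests or Mann–Whitney tests for continuous variables. The same section uses couples as the unit for the frequency of increased chance results and for reproductive decisions, so participant and couple are not used interchangeably.

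**Where the outcome is decided.** Section 2.6.3: "For a couple to access RGCS through the study, the full enrollment process must be completed by both reproductive partners". On non-completion: "If enrollment is completed but the RGCS mouth swab kit is not returned, the couple is recorded as having chosen not to complete RGCS".

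**How records arise.** One member opens the portal and the other is then emailed a link. After that, "Both reproductive partners complete the full enrollment process in parallel in their own time". Section 2.5.4 adds: "Each couple accesses the portal with a unique access code, linked to their rHCP".

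The article mentions no couple-level model, clustered or robust standard error, GEE or random effect for this comparison.

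**The concern.** If both partners must complete the process before either is screened, the outcome cannot differ between two enrolled partners. The second partner's row then adds no new information about the outcome. For a covariate that is also common to the couple, it is a copy of the first row. Ordinary chi-squared tests and logistic regression count that copy as a new observation.

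The covariates most affected are those that bear on equity of access: region, public or private setting, socioeconomic quintile and pregnancy status. The article gives access as a main reason for the program (Section 1) and says results inform a public funding application (Section 2.7). The p < 0.1 selection rule compounds the problem, because it uses the same uncorrected tests to decide what enters the model.

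A second, separate question is who is counted. A couple that proceeds always supplies two records, one from each sex. A couple that stops early may leave only the record of whoever opened the portal. The article does not say how such couples enter a comparison of participants.

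**Working it through.** The article gives no sample size, power or standard error for this comparison, so there is no stated figure to reproduce.

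**Inputs from the article**
- Outcome identical for both partners: within-couple outcome correlation ρ_y = 1 (Section 2.6.3).
- Up to two records per couple, taking the two genetic parents, one male and one female (Sections 1 and 2.6.3).
- Screening threshold 0.1 (Quantitative Analysis). Significance level 0.05 (stated under Psychosocial Outcomes; assumed to apply here).

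**Assumptions, not in the article**
- Within-couple covariate correlation ρ_x, from 0 to 1.
- Share L of non-proceeding couples that leave one record, from 0 to 1.
- Share F of those lone enrollers who are women, 0.5 to 0.9.
- For the simulation: 1000 couples, 70% proceeding, 1500 replicates, null covariate.

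**Step 1. Two records from every couple.** Design effect DE = 1 + (2 − 1)·ρ_y·ρ_x = 1 + ρ_x. Ratio of naive to true standard error = 1/√DE. True error = 2·(1 − Φ(z/√DE)), with z = 1.960 or 1.645.

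| ρ_x | DE | SE ratio | True error at 0.05 | True error at 0.10 |
|---|---|---|---|---|
| 0 | 1.00 | 1.00 | 5.0% | 10.0% |
| 0.25 | 1.25 | 0.89 | 8.0% | 14.1% |
| 0.5 | 1.50 | 0.82 | 11.0% | 17.9% |
| 0.75 | 1.75 | 0.76 | 13.8% | 21.4% |
| 1 | 2.00 | 0.71 | 16.6% | 24.5% |

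For ρ_x = 1: 1.960/√2 = 1.386, two-sided p = 0.166. Simulation of ordinary logistic regression gave 18.4% at ρ_x = 1 and 11.5% at ρ_x = 0.5. The Monte Carlo standard error at 16.6% is √(0.166 × 0.834/1500) ≈ 1.0 point, so this agrees with the formula. The rate does not depend on the number of couples, so the target of 8350 couples does not cure it.

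**Step 2. Some non-proceeding couples leave one record (ρ_x = 1).** Simulated error at nominal 5% was 13.9% with L = 0.5 and 6.4% with L = 1. A rough check uses the variance of a difference in means with 700 proceeding and 300 non-proceeding couples.
- L = 0.5: naive 1/1400 + 1/450 = 0.00294. True 1/700 + (150×4 + 150×1)/450² = 0.00513. SE ratio 0.756, error 13.8%.
- L = 1: naive 1/1400 + 1/300 = 0.00405. True 1/700 + 1/300 = 0.00476. SE ratio 0.922, error 7.1%.

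**Step 3. Couple-clustered standard errors.** Across all simulated scenarios the error at nominal 5% was 3.8% to 6.1%.

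**Step 4. Sex.** Couples that proceed are half women by design. The odds ratio for not proceeding, women against men, is [(1 − L) + L·F]/[(1 − L) + L·(1 − F)].
- L = 0, any F: 1.00.
- Any L, F = 0.5: 1.00.
- L = 0.5, F = 0.6: 0.80/0.70 = 1.14.
- L = 0.5, F = 0.75: 0.875/0.625 = 1.40.
- L = 0.5, F = 0.9: 0.95/0.55 = 1.73.

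The article gives neither L nor F.

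**The case against.** **The variance estimator is not stated.** The article names logistic regression but no standard error. The word independent in "unadjusted logistic regressions for categorical outcomes, and independent, two-tailed" belongs to the t-tests, and the list of univariable methods is open-ended. A couple-clustered logistic model would fit the sentence, and a full analysis plan may specify one. This stands in part: the article does not say that partners are treated as independent in the regression. But it does fix the participant as the unit, the tests and the selection rule. Standard chi-squared and Fisher tests make no allowance for pairs, so the combination as written is unsuited to this outcome.

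**Standard errors are not too small across the board.** Correct. There is no inflation for a covariate uncorrelated within couples. For sex, which always differs between partners, the naive standard error is too large when both are recorded. The 16.6% is a ceiling.

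**A reader might infer that the design itself creates a sex association.** The documents do not support this. With both partners recorded, the sex odds ratio is exactly 1.00. An artefact needs lone records among non-proceeders and also an unequal sex split among them. Section 2.6.3 allows the first without giving its frequency, and nothing gives the second. If sex passed the p < 0.1 screen, adjusting for it would also limit carry-over to sex-related covariates.

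**Point estimates.** Couple clustering affects precision and does not in itself bias the odds ratios. The descriptive uptake figures are not changed by it. Both points stand.

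**Providers.** Couples are nested in recruiting providers, but the article gives no intraclass correlation or couples per provider, so no size can be put on that layer.

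**Conclusion.** The concern holds in a limited form. The outcome is the couple's, the stated unit is the participant, and the stated methods make no allowance for the pairing.

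The consequence is understated standard errors for covariates that partners share or that correlate positively within couples. If ordinary standard errors are used and both partners are recorded, true error at a nominal 5% lies between 5% (correlation 0) and about 16.6% (fully shared). The p < 0.1 screen passes between 10% and 24.5% of null covariates. For a fully shared covariate the error falls to roughly 14% if half of the non-proceeding couples leave one record, and to 6–7% if all do, with 70% of couples assumed to proceed. These are univariable figures; in an adjusted model the relevant correlation is what remains after the other covariates.

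Confounding of sex, and of sex-related covariates, with who enrolled first is possible, but its size is unknown. The odds ratios of 1.14 to 1.73 rest on assumed inputs (half of non-proceeding couples leaving one record, 60–90% of those women), and the value is 1.00 if lone enrollers are evenly split. It is a reason to define how one-partner couples enter, not evidence that the result will be wrong.

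**What to change.** State the unit of the uptake comparison. Either option would do:

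1. **One row per couple.** Include each eligible couple with research consent; the outcome is RGCS done or not. Use couple-level covariates, plus the initiating partner's characteristics where collected. Counting every couple that opened the portal would be wrong, because it would class ineligible or non-consenting couples as not proceeding. In the portal sequence of Section 2.5.4 demographics follow research consent, so some early leavers will lack them. Say how they are handled.
2. **Keep participant rows** with couple-clustered standard errors, and state how couples with one enrolled partner enter and how sex is then interpreted.

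Apply the same unit or clustering to the univariable p < 0.1 screen. Also cluster on the recruiting provider. Couples sit within providers, so provider-level clustering also covers the pairing of partners.

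The cost is analysis wording only, since the access code already links each couple to its provider. Confidence intervals for shared covariates will be somewhat wider, and fewer of those covariates will pass the screen.

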#### 2.6.2. Inviting People to Take Part in Mackenzie’s Mission

After completing the study’s HCP education module, rHCPs began inviting couples who met the eligibility criteria to take part in the study. The rHCP makes this offer to one or both members of the couple—whoever attends the healthcare appointment. Potential participants are informed the study is investigating people’s views and perspectives about RGCS and that participation involves an offer of free screening. If the offer to take part is accepted, they are given a study invitation/test request form and are asked to follow the instructions on the form to enroll in the study online. The rHCP emphasizes that the purpose of the study is to understand the perspectives of those offered RGCS and that those who do not want to undergo RGCS, or are unsure, are welcome to participate and share their views. Those who decline the invitation to take part are provided with a short, optional decliner survey, including the option to leave their contact details to be invited for an interview, which they are asked to complete and return at the clinic reception. Those who do not complete this survey decline all involvement in the study. Where an rHCP identifies that a participant would benefit from enrolling via a modified enrollment pathway, or where a potential participant requests support to enroll, contact is made with the local study team who facilitate enrollment.

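### The model of who goes on to screening is set on participants although proceeding is a couple event: paired rows make standard errors too small, and rows per couple depend on the outcome

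*Protocol article*

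**What the plan says.** Under Quantitative Analysis (section 2.7.1) the article sets the comparison on individuals: "A comparison between participants who had RGCS and participants who did not proceed with RGCS after initiating enrollment". As to method, the article says that this "will be performed using multivariable logistic regression, adjusting for significant covariates", where significant means p < 0.1 in univariable analysis. The univariable tools listed there (chi-squared, Fisher exact, unadjusted logistic regression, independent t-tests, Mann–Whitney) all treat rows as independent. The couple is not mentioned in the description of this model.

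Section 2.6.3 describes how enrollment works:

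- It starts with one person: "one member of the couple accesses the online participant portal via a web link and enters the unique access code".
- That person gives the partner's contact details, and it is then the partner "who is automatically emailed a link to create their own account in the participant portal".
- Each partner thus has a separate record, as the next step shows: "Both reproductive partners complete the full enrollment process in parallel in their own time".
- Screening depends on the two of them together: "For a couple to access RGCS through the study, the full enrollment process must be completed by both reproductive partners".
- If enrollment is complete but the kit is not returned, "the couple is recorded as having chosen not to complete RGCS". Incomplete enrollment, in contrast, is recorded for participants.

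Section 2.6.2 says of the invitation: "The rHCP makes this offer to one or both members of the couple". It does not say which partner usually attends or registers first. RGCS uptake is a separate descriptive outcome, with no unit stated.

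**The concern.** Whether screening took place is the same for both partners by design. Two things follow if participants are the rows.

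First, every couple in which both partners registered supplies two rows with one outcome between them. For covariates that partners share, such as area socioeconomic quintile or pregnancy status, the second row adds no information, yet ordinary logistic regression counts it as new. The p < 0.1 screen then passes too many null covariates into the final model.

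Second, a person whose partner never registers can only be a non-proceeder. The number of rows a couple contributes therefore depends on the outcome being modelled. A willing registrant is also analysed as if his or her own characteristics explained the partner's inaction.

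This is the only multivariable model the article names for who does and does not go on to screening. Acceptability is part of the primary aim, and offer and uptake are listed objectives (section 2.2).

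**Working it through.** The article gives no uptake, odds ratio or power figure for this comparison, so there is none to reproduce. The quantities below marked as assumed are not in the document.

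**Inputs**

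- From the article: participants as the unit; screening requires both partners; screen at p < 0.1. The 0.05 level is stated under Psychosocial Outcomes and is assumed to apply here too.
- Assumed: u, the share of couples that proceed; f, the share of non-proceeding couples with one registrant; w, the share of lone registrants who are women; rho, the within-couple correlation of a covariate.

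**1. Paired rows**

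With two rows per couple and identical outcomes, the model's standard error is too small by a factor of √(1 + rho). The true rejection rate for a null covariate is 2 × [1 − Φ(z/√(1 + rho))].

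| Case | Nominal 5% | p < 0.1 screen |
|---|---|---|
| Shared covariate (rho = 1), all couples paired | 1.96/√2 = 1.386, so 16.6% | 1.645/√2 = 1.163, so 24.5% |
| rho = 0.3, all couples paired | 1.96/√1.3 = 1.719, so 8.6% | 1.645/√1.3 = 1.443, so 14.9% |
| rho = 0 | 5% | 10% |

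A 95% interval for a shared covariate would cover about 1 − 0.166 = 83% of the time when all couples are paired.

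Simulation (2000 runs of 1000 couples, u = 0.7, rho = 1) gave 16.6% and 23.8% with all couples paired. With f = 0.5 and w = 0.9 it gave 13.6% and 21.2%. With one record per couple, rejection at nominal 5% was 4.2% to 4.9% over all scenarios run.

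**2. Lone registrants and sex**

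Per couple, women contribute u proceeding rows and (1 − u)(1 − f + fw) non-proceeding rows. Men contribute u and (1 − u)(1 − f + f(1 − w)). The odds ratio for proceeding, women versus men, is therefore

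(1 − fw) / (1 − f(1 − w)),

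which does not depend on u. At f = 0.5:

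- w = 0.5: 0.75/0.75 = 1.00
- w = 0.7: 0.65/0.85 = 0.76
- w = 0.9: 0.55/0.95 = 0.58

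No true sex effect is possible here, because the outcome is common to both partners.

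**3. Proportion proceeding, if counted on participants**

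The proportion is 2u / [2u + (1 − u)(2 − f)]. At u = 0.7 and f = 0.5 it is 1.4/1.85 = 0.757 instead of 0.70. At f = 0 there is no distortion.

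**The case against.** The strongest reply is that the article uses the word participants loosely. Section 2.6.5 speaks of participants receiving an increased chance result, although only a couple result is issued. On that view row structure and clustering belong to a fuller plan that is not shown. Couple-clustered errors there would indeed repair the standard errors. They would not repair the outcome-dependent number of rows, and the unit that the article does name is the individual, alongside tests that assume independence.

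A second reply is that lone registrants may never reach the model. Table 1 excludes couples in which only one member agrees to take part, reminders and phone calls pursue incomplete enrollments, and demographics come after research consent, so very early drop-outs have no covariates. This limits how many there are. But the first member answers the eligibility questions and opens an account before the partner is contacted, and the comparator is defined by having initiated enrollment. Nothing removes these people from it.

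Two stronger readings are tempting. A reader might infer that reported uptake will be overstated. The article does not support this: uptake is a separate descriptive outcome with no unit given, the regression does not estimate it, and the recruitment target is counted in couples. A reader might also infer that a false sex effect is built in. It needs sex among the covariates, which the comparison does not name, and lone registrants who are mostly of one sex. The invitation goes to whoever attends, which makes imbalance plausible, but no split is stated, and at 50:50 the odds ratio is 1.00.

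The two-rows-per-couple picture is also simplified: the donor pathway can involve more people.

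**Conclusion.** The point holds in this form: the unit of the regression does not match the level at which its outcome is determined. The understated standard errors follow from the text wherever both partners enter and the covariate is positively correlated within couples. Their size depends on that correlation and on how many couples are paired: for shared covariates, roughly 14% to 17% rejection at nominal 5% and 21% to 25% at the screen over the cases examined. The dependence of row count on outcome holds whenever any lone registrant is in the comparator; how many there are is unknown. The sex association is a conditional risk, and inflated uptake is a consequence only of a counting rule that the article does not state.

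This should be corrected before analysis. It is one comparison in an observational mixed-methods study whose acceptability question also draws on surveys and interviews, so it does not undermine the study as a whole.

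**What to change.** Fit the model with one record per couple that initiated enrollment, using the access code that already links partners. Use couple-level covariates plus characteristics of the first registrant, defined the same way for every couple. Taking first-registrant data only where the partner is missing would make the covariate definition itself depend on the outcome. State couples as the denominator for uptake, and report couples with a lone registrant as a separate group.

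If a participant-level model is kept, weight each couple to a total of 1, use couple-clustered errors, and do not interpret sex. Weighting restores the proportion proceeding but not the sex balance: at f = 0.5 and w = 0.9 the weighted odds ratio is (0.25 + 0.05)/(0.25 + 0.45) = 0.43.

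The change is to analysis wording and needs no new data. It costs rows and gives wider intervals, and second-partner characteristics leave the main model.
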